## 1.2 Investigational Agent

(see Investigator's Brochure)

### **Class**

In vivo diagnostic agent.

### **Structure**

The SGM-101 active ingredient is a covalent conjugate of the SGM-Ch511 anti-CEA chimeric monoclonal antibody with the fluorochrome BM-104 (Figure III.1-1). The BM-104 fluorochrome is conjugated to free amino groups of the antibody via an amide bond.

[figure not shown]

Figure Schematic representation of the SGM-Ch511-BM-104 conjugate.

The SGM-101 drug substance presents as a mixture of fluorochrome-antibody conjugate species of different conjugation levels, ranging from 1 to 6 BM104 molecules per antibody and of unconjugated species. The human constant domains of the antibody are of the G1m3 allotype for the heavy chains and Km3 for the light chains.

### **General properties**

The SGM-Ch511-BM-104 conjugates are characterized by peaks of absorbance at 280 nm (antibody) and 685 nm (fluorochrome). Excitation and emission wavelengths peaks of SGM-101 are 686 and 704 nm, respectively.

### **Physical form**

The SGM-101 drug substance presents as a 5.0 mg/mL solution of the active ingredient in 10mM KH2PO4, 10 mM Na3citrate, 300 mM arginine, 0.02% Tween-20, pH 6.0.

## **Non-Clinical Pharmacology, Pharmacokinetics And Toxicology**

### *Pharmacology*

Non-clinical pharmacology studies have demonstrated SGM-101's efficacy in binding to human CEA expressing cells *in vivo* in terms of specificity, sensitivity and targeting scope using four different xenografted or transgenic mouse models.

SGM-101 allowed *in vivo* identification of tumor nodules overexpressing CEA in all models tested, regardless of the location of tumors (including in the peritoneal cavity in peritoneal carcinomatosis mouse models, subcutaneously, in the cecum, pancreas or breast in orthotopic tumor models and in the liver in metastatic models) and of their origin (colorectal, pancreas or breast), confirming the targeting ability of the anti-CEA antibody.

In addition, a high level signal-to-noise ratio allows the detection of very small nodules invisible to the naked eye, even for an experienced investigator.

Moreover, GLP-compliant safety pharmacology studies demonstrated that intravenous SGM-101 administration did not lead to any adverse effects neither on the central and peripheral nervous systems in Wistar rats, nor on the cardiovascular and respiratory functions in Beagle dogs at dose levels of up to 40 mg/kg (240 mg/m^2) and 20 mg/kg (400 mg/m^2), respectively.

### *Pharmacokinetics and metabolism*

*In vitro* stability studies in human plasma at 37°C have confirmed the stability of the amide bonds linking the BM-104 fluorochrome to the antibody.

*In vivo* studies conducted in human CEA-expressing mouse models have shown similar pharmacokinetic profiles as in wild type strains; CEA expression in this transgenic model is exclusively apical, with the antigen not being accessible to circulating SGM-101. Tissue distribution was also comparable in transgenic human CEA-expressing mice and in wild type animals.

SGM-101 was shown to be rapidly eliminated in immunosuppressed mice bearing human intraperitoneal tumors overexpressing CEA and in normal Swiss mice, with remaining SGM-101 levels of less than 10 % of the injected dose, 10 days after injection.

Toxicokinetic evaluation performed in Wistar rats treated intravenously at 5, 20 or 40 mg/kg/day showed that plasma SGM-101 levels increased with dose in an almost

proportional manner. Exposure of SGM-101 was slightly higher in males than in females at the highest dose level.

Preliminary analysis of the pharmacokinetic data from the FIH clinical trial indicates that SGM-101 maximal serum concentrations are usually reached at or close to the end of the infusion and decrease progressively thereafter, with a mean  $t_{1/2}$  of approximately 30 h regardless of the dose level (range of values between 16.9 and 36.3 h). From 5 to 12.5 mg, exposure tends to increase with dose but appears to remain unchanged between 12.5 and 15 mg.

### *Safety*

Toxicity studies conducted with SGM-101 in Wistar rats and in Beagle dogs showed that the drug is well tolerated up to the maximal dose tested of 40 mg/kg per day (85-fold the intended maximum clinical dose) in rats and 5 mg/kg (10-fold the intended maximum clinical dose) in dogs, with minor and transient signs of an infusion reaction at higher dose levels in the latter.

A tissue cross-reactivity study of SGM-101 conducted on a panel of 42 human frozen tissues and blood smears confirmed on-target only binding of SGM-101. BM-104 fluorochrome did not exhibit any signs of toxicity at 3.4 mg/kg (140-fold the maximal anticipated clinical exposure) in Wistar rats and was non-mutagenic in the Ames test.

To date no adverse event related to the study drug has been reported in the ongoing clinical trials, at dose levels ranging from 5 to 15 mg.

## **1.3 Preclinical Data**

(See Investigator's Brochure)

The first use of a fluorescent anti-CEA antibody conjugate was described by the team of Andre Pelegrin under *ex vivo* conditions in patients with colorectal tumors, opening the possibility of such immunodetection in the clinical field (16). Further studies allowed the detection of submillimeter tumor nodules in a murine peritoneal carcinomatosis model (17).

Preclinical evaluation of several CEA-targeting near-infrared fluorescent tracers has been described in the past few years, displaying a good tumor-binding of the tracers (18, 19). Complete resection of human colon cancer was also achieved by fluorescence-guided surgery in an orthotopic nude mouse model, resulting in decreased recurrence and increased survival (19). Fluorescence-guided surgery using a fluorophore-conjugated-anti-CEA antibody to visualize tumors also showed promising results in preclinical orthotopic models of human pancreatic cancer, with

both an improvement of surgical resection and an increased survival of the animals (20).

SGM-101 is a CEA-specific chimeric antibody conjugated to a fluorophore emitting NIR fluorescence around 700 nm. After injection to the patient prior to surgery, the antibody conjugate binds to CEA-overexpressing tumor tissue. By using a NIR fluorescence imaging system, the surgeon can visualize the tumor and detect even small-size nodules invisible to the naked eye, enabling real-time guidance during surgery.

Preclinical studies showed that SGM-101 binds to CEA-positive CRC-cells following intravenous administration and that even small peritoneal metastases can be visualized with a dedicated NIR imaging system, suggesting it to be a worthwhile candidate for clinical application (21).

SGM-101 offers major diagnostic improvements compared to routine surgery such as the clear delineation of tumor masses within a normal environment, the detection of a subclinical carcinomatosis in high-risk patients, or the assessment of residual disease allowing an adapted postoperative treatment.

These properties could enable a more complete surgical resection of tumor lesions and subsequently greatly enhance the patient's prognosis.

## 1.4 Clinical Data

To date the efficacy of SGM-101 has been evaluated in 2 clinical studies: a first-in-human trial that was initiated in France (SGM-CLIN01) in advanced cancer patients presenting with peritoneal carcinomatosis originating from gastrointestinal malignancies, and a second trial (SGM-CLIN02), in the Netherlands, for the delineation of pancreatic and colorectal tumors. Patient enrollment is complete for the SGM-CLIN02 study. These clinical studies are further described below.

### **Clinical Phase I: Safety Of SGM-101 In Patients With Peritoneal Carcinomatosis From CEA Overexpressing Gastrointestinal Cancer (Study # SGM-CLIN01 / Protocol # ICM-URC-2014/35 / # EudraCT : 2014-004017-87.)**

A first-in-man open-label Phase I study was conducted in Montpellier, France (protocol N°ICM-URC-2014/35) to assess the safety of a single intravenous administration of SGM-101 in patients with peritoneal carcinomatosis from CEA-over-expressing gastrointestinal cancers.

Patients were enrolled according to a 3+3 dose escalation scheme at five dose levels: 5 mg, 7.5 mg, 10 mg, 12.5 mg and 15 mg (cohorts 1 to 5). Patients were administered SGM-101 24 hours prior to surgery, and an additional treatment group at the 15 mg dose level was included in order to assess administration 48 hours prior to surgery (cohort 5 pts).

Fifteen patients were enrolled in the study as part of the dose escalation (3 per dose level). Three additional patients were enrolled at the 15 mg dose level according to the second administration scheme (*i.e.* 48 hours prior to surgery).

Visibility and background were assessed by two different and independent surgeons using fluorescent SGM-101. The two surgeons evaluated the peritoneal carcinomatosis index (PCI) without then with fluorescence, to check for the presence of additional fluorescent lesions. However, only very few efficacy data were reported in the study. Only 8 out of 18 patients underwent resection of carcinomatosis because some patients were considered unresectable during surgery due to the extent of carcinomatosis and other patients were not resected because no peritoneal carcinomatosis was confirmed during surgery, whether without or with fluorescence. And, of the 8 patients who were resected, only 3 were evaluable for efficacy due to problems with the NIR camera used in this first study so that given this small sample no conclusion was reached in regard to efficacy.

**Clinical Phase I/II : Safety of SGM-101 in Patients with Cancer of the Rectum or Pancreas (Study # SGM-CLIN02 / Protocol # CHDR1517 / EudraCT # : 2015-003281-88)**

This open-label, ascending single dose study was performed to explore the safety, tolerability, pharmacokinetics and performance of SGM-101 in patients with colorectal and pancreas cancer. This study was a collaborative project between the department of surgery of Leiden University Medical Center (LUMC), Catharina Hospital Eindhoven (CZE), Erasmus University Medical Center (EMC) and the Centre for Human Drug Research (CHDR), The Netherlands. In this report 75 patients (46 males, 29 females), with primary, recurrent or metastasized colorectal cancer (n=61) and pancreas cancer (n=14) were included and analyzed. Five different doses of SGM-101 were evaluated: 5 mg (7 patients), 7.5 mg (10 patients), 10 mg (39 patients), 12.5 mg (9 patients) and 15 mg (10 patients) and dosed at least 24 hours before the planned surgery. The choice for period of at least 24 hours between dosing and surgery was based upon the observations in animals that showed that sufficiently strong signals were reached between 24 and 72 hours. In the study the dosing period varied between 2-6 days before the scheduled surgery, where 4 days prior to surgery showed the most favorable results.

Overall, all doses up to 15 mg SGM-101 were well-tolerated. None of the included patients experienced an allergic reaction or TEAE that was considered of clinical importance or led to discontinuation of the study. No trends or changes of clinical importance were noted in the vital signs, ECG, or laboratory parameters after SGM-101 administration. Hence, there appears to be no safety concerns associated with iv administration (30 minutes infusion) of SGM-101 at doses up to 12.5 mg in pancreas patients and 15 mg in colorectal cancer patients.

The performance of SGM-101 in the study was evaluated on the basis of the obtained fluorescence imaging results during surgery and the concordance with the pathology.

In the study, a clear benefit of using SGM-101 was found in the colorectal cancer patients where SGM-101 was beneficial in the identification of additional lesions that were clinically not suspect for malignancy. In the colorectal patients, additional lesions were found in 8 patients. A total of 21 additional lesions were identified by using intraoperative fluorescence; 20 lesions in the 10 mg SGM-101 group (dosed 4 days prior to surgery) and 1 lesion in the 12.5 mg SGM-101 group (dosed 4 days prior to surgery). The mean TBR of these additionally identified lesions was 1.7. Importantly, these lesions were confirmed as malignant during pathology review.

The analyzed images showed that the mean intraoperative TBR had the highest mean value of 1.7 in the 10 mg SGM-101 dose group when compared to the other dose levels. Higher dose did not always result in a higher TBR, most likely because the background fluorescence signal was also increased. Furthermore, the results show that the dose level 10 mg SGM-101 has the most optimal sensitivity (97%) and specificity (52%) combination along with an adequate negative predictive value (93%). A possible shortcoming of the study is that the amount of patients included in each dose level is not equal resulting in a sub-optimally powered comparison. The additional cohort which was implemented to evaluate a delay in the injection time to 6 days prior to surgery did not result in higher TBR values.

A noteworthy finding is that 10 mg SGM-101 has a high negative predictive value (93%). This opens the possibility that clinical decisions to resect tissue can be changed based on the (fluorescent) findings during surgery. Nevertheless, during these clinical decisions the possibility for false negatives should always be taken into account, even though the study only had 3 false negatives; 3 of the 184 lesions (~2%).

In the pancreas cancer patients, intraoperative fluorescence imaging of pancreas cancer was feasible as fluorescence could be detected in the primary tumors as well as the metastases. Despite the suboptimal intrinsic characteristics of pancreas cancer, including poor vascularization, the results showed that SGM-101 can reach and bind to CEA-expressing tumor cells. The TBRs in the pancreas cancer patients were more ambiguous when compared to the CRC patients. This can possibly be explained by the histopathology of pancreas cancer, with solitary ducts of tumor cells in preexistent normal pancreatic tissue and a remarkable desmoplastic stroma, which could make the fluorescence pattern more sparse than with other tumor types. Most of the pancreas cancer patients were dosed with 7.5 mg SGM-101 and the highest mean intraoperative TBR was calculated in the 5mg SGM-101 group.

The calculated TBRs provided insight on the performance of the different dose levels studied in CRC and pancreas cancer patients. It is considered that the intraoperative TBR should be leading, as the decision making to resect tissue (based on

fluorescent status or not) is done during surgery. However, decision making on intraoperative fluorescence only has its drawbacks for instance for deep-seated tumors that cannot readily be visualized because of the limited penetration depth of fluorescent light (maximally 1 cm) or for tumors that are in an anatomic position that precludes proper imaging. Additionally, overlying tissue and blood in the surgical field can also cause intraoperative false-negativity. It is therefore that ex-vivo (back table) results should also be taken into account. In the majority of lesions, fluorescence was not visible or measured intraoperatively, but fluorescence could be clearly detected after resection, which was subsequently confirmed to be malignant by pathology review. In these situations, fresh frozen sections are of added value.

It was therefore decided to present the final conclusion on concordance between pathology results and the combined fluorescence results (in-vivo and ex-vivo fluorescence). Several considerations should be taken into account when using this approach. Combining in vivo and ex vivo imaging to assess concordance may diminish the chance that a finding is labelled false negative, while it is not detected during the surgical procedure itself. However, as back table (ex vivo) results may provide important information during the surgery on the completeness of resection (margin-assessment), it felt justifiable to follow this approach. In addition, caution should be used when combining in-vivo and ex-vivo results. During back table imaging, surrounding tissue plays a lesser role since only the excised lesion is being assessed, which can possibly influence the fluorescence emitted.

A relative high amount of false positive lesions were found in the CRC patients. Although a definitive explanation is not readily available, it was noted that a majority of these false positives were found in the reproductive organs (such as ovaries and vesicula seminalis). Apparently, these organs show a high binding (absorption) capacity for SGM-101. Why these organs were fluorescent during surgery, without containing tumor cells is not yet explained. There are, however, no indications that gender-based dosing is necessary.

Overall, according to the current descriptive results, the calculated TBRs and concordance show that 10 mg SGM-101 4 days prior to surgery is a reasonable choice and possibly the most favorable treatment for intraoperative fluorescence imaging of patients with colorectal cancer. For pancreas cancer, the highest intraoperative TBR was seen in the 5 mg SGM-101 dose level group. CEA was chosen as a suitable target for fluorescence imaging of colorectal and pancreas cancer. The study confirmed its potential and demonstrated that both colorectal and pancreas cancer, including metastases of both tumor types, can be visualized using intraoperative fluorescence imaging with SGM-101.

## **2 Study Objectives**

### **Primary Objective**

The primary study objectives are to assess the sensitivity and specificity of SGM-101 in detecting non-small cell lung carcinomas during surgery.

### 3 Study Design

#### 3.1 General Design

Subjects will be seen in a General Thoracic Surgery clinic. If they have a lung nodule that is suspicious for a lung non-small cell lung cancer, they will be a candidate for the operation. From our prior experience, we have an 90% positive predictive value based on CAT and PET scans that a subject with a suspected lung cancer will in fact have lung cancer. The subjects with lung and pleural nodules will be prospectively consented to participate in this trial. There will be no randomization or control group and only subjects previously scheduled to undergo surgery will be eligible to participate. We anticipate a 24-month period will be necessary to reach our accrual goal of 20 subjects.

After obtaining informed consent, subjects will receive a one-time dose of 5 to 10 mg of SGM-101, up to 5 days prior to the planned operation. As a prophylactic measure, we may recommend giving 25 mg of IV Benadryl to the subject prior to the infusion of SGM-101 to ensure possibility of allergic reaction is absolutely minimized. This will be at the discretion of the principal investigator. The goal of surgery in subjects is to remove the nodule and lymph nodes in concern. During surgery, we will take images with an intra-operative camera system. Imaging will take place prior to surgical resection to record the localization of tumors, and post-resection to document the visualization of any residual tumor. All documenting of nodules will take place in an electronic report form.

Our analysis will be the following:

| Data Analysis of a Diagnostic Test |                    | Test result                                        |                                                   | Data Analysis                                                             |
|------------------------------------|--------------------|----------------------------------------------------|---------------------------------------------------|---------------------------------------------------------------------------|
|                                    |                    | True
(accept $H_0$ )                            | False
(accept $H_A$ )                          |                                                                           |
| Disease present
("The Truth")   | True
( $H_0$ )  | TP
( $1 - \beta$ )                              | FN
(type 2 error = $\beta = 1 - \text{sens}$ ) | $\text{sensitivity} = \frac{TP}{TP + FN}$                                 |
|                                    | False
( $H_A$ ) | FP
(type 1 error = $\alpha = 1 - \text{spec}$ ) | TN
( $1 - \alpha$ )                            | $\text{specificity} = \frac{TN}{TN + FP}$                                 |
| Data Analysis                      |                    | $PPV = \frac{TP}{TP + FP}$                         | $NPV = \frac{TN}{TN + FN}$                        | $\text{Accuracy} = \text{efficiency} = \frac{TP + TN}{TP + TN + FP + FN}$ |

True positive = fluorescent nodule, pathology is cancer

False positive = fluorescent nodule, pathology is no cancer

True negative = not fluorescent nodule, pathology is no cancer

False negative = not fluorescent nodule, pathology is cancer

Cohort 1: Our first 10 subjects will be a feasibility trial. We will discover whether lung non-small cell lung cancers fluoresce based on the intraoperative images. The surgeon will look at the images during surgery to determine if the tumor is glowing or not. Based on prior experience, we will be cautious for false positives. In our first 10

subjects, if we have 5 or more subjects with a false positive, then we will review the data prior to proceeding. If we have a high false positive rate, then we will likely not proceed because the clinical value of the fluorescent probe is minimal. (Of note, if the first five consecutive patients have false positives, we will stop the study and analyze the data carefully before we will consider proceeding).

Cohort 2: If the first 10 subjects show no significant false positives, then we will perform another 10 subjects. The primary goal will be to determine (a) how many non-small cell lung cancers are detected by intraoperative imaging? Additional data will be collected to determine (b) how deep the imaging system can see into the lung organ, (c) can metastatic cancer cells in lymph nodes and satellite nodules be detected? (d) if the surgeon mistakenly cuts through the tumor, will the intraoperative imaging detect a positive margin? In this cohort, we will not make any clinical decisions to jeopardize the patient or remove significantly more than the intended operation. We will collect more data in this cohort for analysis.

During Imaging, if the removal of a fluorescent lesion does not change the magnitude of the operation, then it can be removed. Until we have more data on the false positive rate of our technology, we will not change the magnitude of the operation based on results from an investigational drug. Lesions that are identified by the surgeon and not the imaging system will be removed at the surgeons' discretion following the standard of care operation.

The duration of surgical procedures to resect thoracic malignancies varies substantially, anywhere from 2- 6 hours or more. It is estimated that visualization of the chest and removal of nodules for the purposes of this study will require an additional ten (10) minutes. Due to potential quenching of the fluorophore, visualization time will be limited to 30 minutes.

The visualization will be conducted with a camera: The Artemis Handheld Camera System-- open-field and laparoscopic-- manufactured by the Quest Medical Imaging. The Artemis has received approval from the FDA for a Phase II ovarian cancer clinical trial in Ohio, The Artemis is registered with the FDA for fluorescence imaging. The Artemis systems are proposed to be non-significant risk (NSR) devices as the devices do not meet the criteria of a significant risk device defined in 21CFR 812.3 (m). Another camera that will be used for visualization is called the Spectropath FLI-10A which is manufactured by Nanjing NuoYuan Medical. The cameras will be stored in the offices in operating room that stores the camera towers and will be used for the surgeries. The camera will be rolled into the operating room by the surgeon performing the case.

There is a chance that being under anesthesia for the additional five (5) to ten (10) minutes could put the subject at an increased risk of having a common side effect associated with anesthesia. These common side effects include, but are not limited to: nausea and vomiting after surgery, sore throat and hoarseness, shivering/chills, confusion, and muscle aches.

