| Study Center(s)                       | Single Center                                                                                                                                                                                                                                  |
| Primary Objective                     | The primary end-point of the study is to determine the sensitivity of SGM-101 in identifying lung nodules when excited by a near-infrared light source.                                                                                        |
| Secondary Objective                   | The secondary objective is to measure the concordance of fluorescence and tumor type.                                                                                                                                                          |
| Number of Subjects                    | We intend to enroll 20 lung cancer subjects in this study.                                                                                                                                                                                     |
| Diagnosis and Main Inclusion Criteria | The study is focusing on subjects presenting with suspected malignancies of the lung and pleura who are considered to be good surgical candidates.                                                                                             |
| Study Product, Dose, Route, Regimen   | SGM-101 is a fluorescent conjugate comprised of a tumor-specific, anti-carcinoembryonic antigen (CEA) monoclonal antibody and a near infrared (NIR) emitting fluorochrome. We will give 5 to 10 mg intravenously 3 to 5 days prior to surgery. |
| Duration of administration            | The proposed dose of SGM-101 to be investigated in this study is 10 mg to be administered intravenously over 30-60 minutes.                                                                                                                    |
| Reference                             | Non-placebo controlled                                                                                                                                                                                                                         |

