## 4 Subject Selection and Withdrawal

### 4.1 Inclusion Criteria

1. Adult subjects over 18 years of age
2. Subjects presenting with a lung, pleural nodule or mass presumed to be resectable on pre-operative assessment
3. Good operative candidate
4. Subject is capable of giving informed consent and participating in the process of consent.

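### Section 3.1, inclusion criterion 2 and the Study Summary describe different populations, so the 20 subjects need not be the suspected-NSCLC patients the objective concerns

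*Protocol*

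**What the plan says.** The descriptions of the population are these.

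- Section 3.1, on candidates: "If they have a lung nodule that is suspicious for a lung non-small cell lung cancer, they will be a candidate for the operation".
- Section 3.1, same paragraph, on consent: "The subjects with lung and pleural nodules will be prospectively consented to participate in this trial". It adds that "only subjects previously scheduled to undergo surgery will be eligible to participate".
- Section 4.1, criterion 2: "Subjects presenting with a lung, pleural nodule or mass presumed to be resectable on pre-operative assessment". The Schedule of Procedures repeats this requirement at Visit 1. None of the exclusions in section 4.2 concerns the type of lesion.
- Study Summary, eligibility row: "The study is focusing on subjects presenting with suspected malignancies of the lung and pleura who are considered to be good surgical candidates". The row on number of subjects instead speaks of 20 people with lung cancer.

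The question asked is narrower. Section 2 gives the primary objective as sensitivity and specificity for NSCLC, and section 3.2 words the efficacy endpoint the same way. The two-by-two definitions in sections 3.1 and 7.1 classify a nodule only as cancer or no cancer on pathology. Section 7.2 sets the denominator at 20, with one nodule per patient.

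Section 3.1 also reports from prior experience that "we have an 90% positive predictive value based on CAT and PET scans that a subject with a suspected lung cancer" will prove to have lung cancer.

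**The concern.** Sites decide eligibility on section 4. As written, a pleural mass, a solitary lung metastasis from another organ or a probably benign nodule all satisfy criterion 2, provided the patient is a good operative candidate. Each takes one of only 20 places.

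Two consequences follow. First, a cancer that is not NSCLC enters the two-by-two table as a true positive or false negative, so the estimate is no longer sensitivity for NSCLC. If such cases are removed afterwards, the denominator is smaller than the stated 20. Second, the share of non-cancer nodules determines how much can be learned about specificity, and whether the false-positive review after the first 10 subjects can be triggered at all. Both depend on which entry description the site applies. The 90% in section 3.1 describes people with suspected lung cancer and gives no information on the wider group.

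**Working it through.** **Step 1. Compare the descriptions.**

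| Place | Site of lesion | Suspicion required |
|---|---|---|
| 3.1, candidates | lung | NSCLC |
| 3.1, consent | lung and pleura | none named |
| 4.1 criterion 2; Schedule | lung or pleura, resectable | none named |
| Study Summary, inclusion | lung and pleura | malignancy |
| Study Summary, number | lung | stated as lung cancer |
| 2 and 3.2, target | lung | NSCLC |
| 3.1 and 7.1, two-by-two table | nodule | any cancer on pathology |

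The inconsistency runs between sections and also within 3.1.

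**Step 2. Does the 90% enter the statistical plan?** Section 7.1 expects 60% of 20 subjects to have fluorescent tumors: 0.60 × 20 = 12, which reproduces its figure without the 90%. The product 0.90 × 20 = 18 appears nowhere. The 90% comes without numerator or denominator, so it cannot be re-derived. It is background experience.

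**Step 3. What the case mix changes.** The protocol gives no cancer share for criterion 2. The shares below 90% are assumptions. With one nodule per subject (section 7.2) and share p:

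- cancers = 20p and non-cancers = 20(1 − p);
- exact (Clopper-Pearson) 95% interval for sensitivity, with about 60% of cancers detected as an illustration;
- exact lower 95% limit for specificity if every non-cancer nodule is dark: 0.025^(1/m), where m is the number of non-cancers. For m = 2, √0.025 = 15.8%;
- P(at least 5 non-cancers in the first 10), binomial(10, 1 − p). A false positive needs a non-cancer nodule, so this is the ceiling on the chance of reaching the review trigger of 5 or more in section 3.1.

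| p | Cancers / non-cancers | Detected; 95% interval | Specificity lower limit | Ceiling on trigger |
|---|---|---|---|---|
| 90% | 18 / 2 | 11; 35.7% to 82.7% | 15.8% | 0.2% |
| 80% | 16 / 4 | 10; 35.4% to 84.8% | 39.8% | 3.3% |
| 70% | 14 / 6 | 8; 28.9% to 82.3% | 54.1% | 15.0% |
| 60% | 12 / 8 | 7; 27.7% to 84.8% | 63.1% | 36.7% |
| 50% | 10 / 10 | 6; 26.2% to 87.8% | 69.2% | 62.3% |

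At 90% the chance of no non-cancer nodule in 20 subjects is 0.9^20 = 12.2%.

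The cancer column counts all cancers. The NSCLC denominator is smaller by every metastasis or pleural tumor among them, and the protocol gives no figure for that.

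**The case against.** The strongest reply is that patients already scheduled for thoracic surgery, and judged good operative candidates, will in practice be mostly suspected lung cancers. Section 7.2 adds that people with more than one nodule are usually not operated on, because that represents metastatic disease. This stands in part. These filters narrow the inflow, so one can say only that the enrolled group need not match the target. They do not exclude a solitary metastasis, a pleural mass or a benign nodule.

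A reader might infer more than the documents support in four ways.

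- **That a planning figure is invalidated.** The 90% feeds no sample-size, precision or stopping calculation. It also concerns lung cancer, not NSCLC, so 18 is not an expected NSCLC count.
- **That section 3.1 requires CT and PET for entry.** It cites the scans only as the basis of the 90%.
- **That section 3.1 flatly opposes criterion 2.** Its consent sentence covers lung and pleural nodules, in agreement with criterion 2.
- **That colorectal metastases would raise sensitivity by a known amount.** Taking 3 of 18 cancers at the 97% in section 1.4 and 15 at 60% gives (3 × 0.97 + 15 × 0.60)/18 = 11.91/18 = 66%. The 3 is invented. The 97% comes from a study whose final concordance combined in-vivo and ex-vivo fluorescence, which section 1.4 itself says may reduce false negatives. It was obtained at one dose level, and nothing shows that it carries over to lung metastases. The 60% in section 7.1 is a share of all 20 subjects; on 18 cancers the same 12 would be 12/18 = 67%. A shift from 60% to 66% is therefore not established.

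It is also fair to say that counting any cancer against an NSCLC objective is a matter of endpoint definition. Restricting the analysis to confirmed NSCLC removes that distortion. It does not settle who fills the 20 places or what denominator remains.

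**Conclusion.** The concern holds in a limited form. The protocol's descriptions of its population disagree. The broadest one, criterion 2, is the operative rule and admits subjects outside the NSCLC question. The any-cancer table and the fixed denominator of 20 then carry them into the primary estimate. The 90% predictive value cannot be assumed for them.

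No number in section 7 changes. The size cannot be fixed from the documents. Over assumed cancer shares from 90% down to 50%, cancers fall from 18 to 10 and non-cancers rise from 2 to 10. The ceiling on the false-positive trigger moves from 0.2% to 62.3%. These figures assume one nodule per subject and independent subjects. Neither the direction nor the amount of any bias in sensitivity is established. For a descriptive pilot this is a matter of making the result interpretable, and it is worth settling because the correction is cheap.

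**What to change.** Reconcile section 3.1, criterion 2 in section 4.1, the Study Summary and the Schedule of Procedures on one population.

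If the broad entry is intended, keep it and do the following:

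- record the pre-operative suspicion at Visit 1 as primary NSCLC, metastasis, pleural lesion or probably benign;
- base the primary NSCLC sensitivity on subjects entered as suspected NSCLC whose pathology confirms NSCLC;
- report other cancers separately, outside that estimate;
- keep benign nodules for specificity;
- replace the fixed denominator of 20 in section 7.2 with a statement that the NSCLC denominator will be below 20.

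There is no need to add a CT or PET entry requirement, which the protocol does not state. The 90% can stay as background if it is labelled as applying to suspected lung cancer only.

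The cost is wording in four places, one data item at Visit 1 and a smaller stated denominator for sensitivity. Narrowing entry to suspected NSCLC is the alternative. It would slow accrual and leave very few non-cancers for specificity, which section 2 also makes a primary aim: about 2 of 20 at a 90% cancer share, with an exact lower limit of 15.8% even if both are negative.
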